# Investigating the impact of London’s ultra low emission zone on children’s health: children’s health in London and Luton (CHILL) protocol for a prospective parallel cohort study

**DOI:** 10.1186/s12887-023-04384-5

**Published:** 2023-11-04

**Keywords:** Children, Cohort, Ethnicity, Air pollution, Lung function, Health impacts, Health inequalities, Costs

## Abstract

**Background:**

Air pollution harms health across the life course. Children are at particular risk of adverse effects during development, which may impact on health in later life. Interventions that improve air quality are urgently needed both to improve public health now, and prevent longer-term increased vulnerability to chronic disease. Low Emission Zones are a public health policy intervention aimed at reducing traffic-derived contributions to urban air pollution, but evidence that they deliver health benefits is lacking. We describe a natural experiment study (CHILL: Children’s Health in London and Luton) to evaluate the impacts of the introduction of London’s Ultra Low Emission Zone (ULEZ) on children’s health.

**Methods:**

CHILL is a prospective two-arm parallel longitudinal cohort study recruiting children at age 6–9 years from primary schools in Central London (the focus of the first phase of the ULEZ) and Luton (a comparator site), with the primary outcome being the impact of changes in annual air pollutant exposures (nitrogen oxides [NOx], nitrogen dioxide [NO_2_], particulate matter with a diameter of less than 2.5micrograms [PM_2.5_], and less than 10 micrograms [PM_10_]) across the two sites on lung function growth, measured as post-bronchodilator forced expiratory volume in one second (FEV_1_) over five years. Secondary outcomes include physical activity, cognitive development, mental health, quality of life, health inequalities, and a range of respiratory and health economic data.

**Discussion:**

CHILL’s prospective parallel cohort design will enable robust conclusions to be drawn on the effectiveness of the ULEZ at improving air quality and delivering improvements in children’s respiratory health. With increasing proportions of the world’s population now living in large urban areas exceeding World Health Organisation air pollution limit guidelines, our study findings will have important implications for the design and implementation of Low Emission and Clean Air Zones in the UK, and worldwide.

**ClinicalTrials.gov:**

NCT04695093 (05/01/2021).

**Supplementary Information:**

The online version contains supplementary material available at 10.1186/s12887-023-04384-5.

## Background

Traffic-related air pollution is associated with adverse health effects across the life course and substantial health inequalities [1, 2]. Children are particularly vulnerable, [1, 3] with adverse effects observed on developmental trajectories and long-term health, including birth outcomes [4] stunted lung growth, [5] delayed cognitive development [6] and increased incidence of psychiatric disorders [7]. Exposure to air pollution during infancy and childhood is associated with increased risk in later life of asthma, pneumonia and chronic obstructive pulmonary disease [8]. Even exposures below legal limit values are associated with disability, disease and death in childhood [1].

Cohort studies have played a key role in identifying these impacts. The ESCAPE meta-analysis of five European birth cohorts showed poor air quality was associated with reduced lung function in pre-adolescent children [9]. The California Children’s Health Study (CHS) showed clinically important deficits of lung growth and function in adolescents [10–13]. Whilst these studies have illustrated associations between adverse responses and air pollutant exposures, it is also notable that downward trends in air pollution have also been shown to deliver health improvements. This was illustrated by the successive children’s cohorts within the CHS (between 1994 and 2011) where the proportion of adolescents with clinically significant deficits in lung function fell as air quality in California improved [14].

There is therefore an urgent need to identify the most impactful policy interventions that improve air quality and deliver health benefits. Low Emission Zones (LEZ), which restrict the entry of polluting vehicles to urban areas, and related Clean Air Zones, have become the dominant public health policy intervention in the effort to improve air quality across Europe [15]. To date, studies evaluating their impact have shown variable effects on road use, [16] exhaust emissions, and air quality, with few identifying clear health benefits [5, 17–24]. A systematic review which evaluated the impact of air quality strategies across Europe on health and health inequalities found negligible effects on respiratory symptoms [23] with only one of 15 the studies identified gathered health data directly from individuals [24]. There was limited evidence for impact of LEZs on air quality in five EU countries (Denmark, the Netherlands, Germany, Italy and the UK) though the health impact of these changes were not addressed [25]. A recent Cochrane systematic review focusing on interventions to reduce ambient particulate matter air pollution and their effect on health identified few studies, with only low or very low grade evidence that interventions targeting vehicular sources improved air quality or health [26].

London implemented its first LEZ from 2008 to 2012, with phased tightening of emission standards in 2008 and 2012. We evaluated its impact, using a sequential cross sectional design, on the health of 2,297 east London primary school children, [5, 27] finding small improvements in air quality (most clearly NO_2_ reductions at the roadside), but no convincing health benefit, such as improvements in lung function or respiratory symptoms.[29] Furthermore, over the study period, we identified significant deficits in participating children’s lung capacity of between 5 and 10%, associated with exposures to traffic-related pollutants.

## Methods

### Primary research question

Does the implementation of London’s ULEZ improve lung function growth trajectories in children of primary school age?

### Secondary research questions

To what extent does ULEZ implementation improve including air quality, specifically reductions in the emissions from diesel vehicles?Does ULEZ implementation result in a reduction in respiratory and allergic symptoms, and respiratory infections in primary school aged children?Does implementation of the ULEZ encourage increased outdoor physical activity, alter travel behaviours and impact on children’s weight and risk of obesity?Does the ULEZ deliver measurable benefits in the perception of quality of life?Does the ULEZ reduce health inequalities, health care use and associated costs?Does SARS-Cov-2 infection affect children’s lung development?

### Outcome measures

#### Primary

Lung growth (post-bronchodilator forced expiratory volume in one second, FEV_1_).

#### Secondary

Air quality, forced vital capacity (FVC), respiratory symptoms, respiratory infections, physical activity, quality of life, health care use and costs, seroprevalence of SARS-CoV-2 antibodies, and a range of respiratory and health economic data.

Details of outcome measures and the timing and means of their collection are given in Table 1.

**Table 1 Tab1:** Outcome Measures

Type	Outcome	Method	Year 1	Year 2	Year 3	Year 4	Year 5	Recording	Analysis
Primary	FEV_1_	Annual health assessment: spirometry	school visit	school visit	school visit	school visit	school visit	Spirometer download	Interaction analysis
Exposures	Air quality: NO, NO_2_, PM10, PM2.5	k-means clustering developed by Font et al.(27)	LAQN* and AURN**	LAQN and AURN	LAQN and AURN	LAQN and AURN	LAQN and AURN	LAQN and AURN	Interaction analysis
Secondary	FVC and other spirometric variables	Annual health assessment: spirometry	school visit	school visit	school visit	school visit	school visit	Spirometer download	Interaction analysis
Secondary	Physical activity and GPS tracking	Annual health assessment: accelerometer and GPS tracker	school visit	school visit	school visit	school visit	school visit	Accelerometer and GPS download	Interaction analysis
Demography / potential confounding variables		Parent-completed questionnaire: (paper or web)	school bag prior to school visit	school bag prior to school visit	school bag prior to school visit	school bag prior to school visit	school bag prior to school visit	Clinical Record Form	Interaction analysis
Secondary	School absence; work absence	Parent-completed questionnaire: (paper or web)	school bag prior to school visit	school bag prior to school visit	school bag prior to school visit	school bag prior to school visit	school bag prior to school visit	Clinical Record Form	Interaction analysis
Secondary	Respiratory and allergy symptoms (ISAAC^+^)	Parent-completed questionnaire: (paper or web)	school bag prior to school visit	school bag prior to school visit	school bag prior to school visit	school bag prior to school visit	school bag prior to school visit	Clinical Record Form	Interaction analysis
Secondary	QOL (CHU9D^++^)	Parent-completed questionnaire: (paper or web)	school bag prior to school visit	school bag prior to school visit	school bag prior to school visit	school bag prior to school visit	school bag prior to school visit	Clinical Record From	Interaction analysis
Secondary	Non-NHS costs	Parent-completed questionnaire: (paper or web)	school bag prior to school visit	school bag prior to school visit	school bag prior to school visit	school bag prior to school visit	school bag prior to school visit	Clinical Record From	
Secondary	Respiratory infection Health care use NHS costs	Data extraction from GP health records	Gathered after year 4 school visits complete	Gathered after year 4 school visits complete	Gathered after year 4 school visits complete	Gathered after year 4 school visits complete	Gathered after year 4 school visits complete	Clinical Record Form	Interaction analysis
Secondary	Health care use NHS costs	Data extraction from GP health records, HES^+++^ data linkage	n/a	n/a	n/a	n/a	Data extraction in year 5	Clinical Record Form/HES data	Interaction analysis
Secondary	SARS-CoV-2 antibodies	Finger-prick blood test	n/a	n/a	n/a	School visit	n/a	Clinical Record Form	Interaction analysis

* LAQN: London Air Quality Network

** AURN: Automatic Urban & Rural Network

^+^ ISAAC: International Study of Asthma and Allergy in Children Questionnaire

++ CHU9D: Child Health Utility 9D score

+++ HES: Hospital Episode Statistics

### Study design

The CHILL study is a prospective parallel longitudinal cohort study performed over 4 years at two separate locations, one impacted by the ULEZ road traffic management scheme and one not. The full study design is outlined in Additional file 1 -Fig. 1.

### Study population and setting

Children (age 6–9 years) are recruited from 44 London primary schools (years 2, 3, 4) with a catchment area within and bordering the Central London ULEZ area, and 41 primary schools (year 2, 3, 4) from the Boroughs of Luton and Dunstable. The Luton area is chosen as a suitable comparison site to Central London due to its broadly similar air quality, demography, and levels of socio-economic deprivation. Whilst it is subject to projected air quality improvements through national government policy, it does not have the ambitious local scale policies being enacted within London. It is also sufficiently distant from London to be free from risk of contamination by effects of the ULEZ. School and participant eligibility criteria are summarised in Table 2.

**Table 2 Tab2:** Eligibility Criteria

	Primary schools	Individuals
**Inclusion criteria**	Any school located within, or whose catchment area includes the Central London ULEZ; or within the Boroughs of Luton and Dunstable.	All children attending a study school, in years 2, 3, or 4 at study inception.
**Exclusion criteria**	Primary schools that are not within the above boundaries outlined above.	Children with learning or physical disabilities sufficient for them to be unable to give informed assent to the study, or to carry out study procedures. Children with major lung disease (not including asthma).

### Study interventions

#### London ultra low emission zone

The Central London ULEZ, implemented on April 8th 2019 uses number plate recognition technology and a daily penalty charge notice issued for vehicles entering this central zone not meeting the set standards – as outlined in Additional File 2 -Fig. 2 It superseded the previous T-charge, which set minimum emission standards of Euro 4/IV for petrol and diesel vehicles and Euro 3 for motorised tricycles and quadricycles, increasing the emission standards to Euro 6 for diesel vehicles. It applies to all vehicles, 24 h a day across the whole year, except for Christmas day. The ULEZ was subsequently extended to the North Circular Road (A406) and South Circular Road (A205) in October 2021 (orange zone), with a London-wide ULEZ for heavy duty vehicles (HDV) within the current LEZ boundary. As a consequence of the first wave of the Corona virus outbreak in the UK, the ULEZ and the Central London Congestion Charging Zone were suspended between the 23rd March − 18th May 2020.

#### Luton: comparison site

Luton’s air quality is influenced by several factors: the presence of major industry (including a motor industry), the transecting M1 motorway and major road A505, and a rapidly expanding international airport, all bringing significant traffic flows into and through the town. Luton has no plans for a Clean Air Zone. It has three designated Air Quality Management Areas. Planned interventions for air quality improvement include a busway, car sharing, public information and advice systems, and provision of charging points for electric vehicles.

### Sample size

We use 90% power and 0.05 significance level to test a 15 ml difference in FEV_1_ growth per year between Central ULEZ and Luton comparison cohorts. For 40 schools/arm with 40 children from any of school years 2, 3, or 4, the study is powered for 15ml per year difference in FEV_1_ growth between the comparison zone and ULEZ. The total target sample size is therefore 3,200 children, comprising 1,600 in the London cohort and 1,600 in the Luton cohort.

### Assumptions

Adjustment for clustering of lung function outcomes within schools, by inflating sample size using an intra-class correlation (ICC) for FEV_1_ in schools calculated from our original ULEZ study (ICC = 0.001).70% success rate in children in classes Y2 and Y3 for a valid reading for FEV_1_.20% attrition per year of follow up, reflecting children moving schools or withdrawing.30% inflation to enable subgroup analysis.

With COVID-19 lockdowns closing schools and leading to loss of data collection during study years 2 and 3, we calculate that addition of a 5th year of data collection with follow up of children moving to secondary schools during study years 4 and 5 will deliver study power as follows:

25% capture of movers to secondary schools retains 80% power.50%, 75% and 100% capture of movers retains over 90% power.

### Recruitment

#### School recruitment

All schools meeting the inclusion criteria are invited to take part and made aware of the study through local media and contact with local leaders and parent groups. An initial invitation email with a link to a short YouTube video summarising the study is sent to headteachers of all schools, [29] followed up by a call from the study Chief Investigator.

#### Child recruitment and informed consent

Informed consent forms are completed by caregivers and children at home, and require opt-in to study components, including elements of the health assessments and access to GP health records and Hospital Episode Statistics (HES) data. The recruitment and informed consent procedure follows a “school bag” approach, facilitated by school staff, Additional file 3 -Fig. 3. Study documents include a QR code link to the study video.

### Patient and public involvement

Patient and public involvement (PPI) in the CHILL study is integral to the study and makes both a formal and informal contribution. Study design is informed by consultation with parents, headteachers, children from the study areas, and community pressure groups such as ‘Mums for Lungs’.

The CHILL Study, as a progression of previous research projects, [5] benefits from an established network of interested public, forming the CHILL study dedicated PPI group. The group aims to ensure that the perspectives and welfare of the participant children, care givers and schools remain at the centre of the study throughout. The PPI group provides: (i) comment and advice on study materials; (ii) supports recruitment and retention in the study; (iii) advises on dissemination of progress and findings and (iv) provides representatives who are members of the Project Management Group (PMG) and Independent Steering Committee (ISC).

Informal PPI between the study team and school staff, children and caregivers is ongoing throughout the lifetime of the project.

### Science outreach education

Central to the CHILL study community outreach strategy is to engage children from participating schools as active participants in science and health research. Most study schools are in areas of socioeconomic deprivation with high proportions of families from Black, Asian and ethnic minority (BAME) heritages. To this end, an interactive science outreach session addressing air pollution and health is delivered by a learning outreach officer to all school classes participating in the study, regardless of how many individual children are taking part in health assessments. Children and class teachers are invited to provide feedback on the sessions to be taken into consideration for future science session planning and involvement. The intention is each year to deliver a fresh outreach session addressing a different aspect of air pollution and health that links to the CHILL core respiratory study, and genetics and cognitive development sub-studies:

Study year 1: Air pollution and your lungs.Study year 2: Air pollution and your genes.Study year 3: Online outreach education resources available to schools.Study year 4: Air pollution, your brain and cognition.Study year 5: CHILL: Air pollution and action for the future.

### Data collection methods

Using different formats and measurement tools (Table 2), data is collected in two ways: (1) directly from children and teachers at health assessments during school visits and (2) from the annual study questionnaire filled out by caregivers returned *via* the school bag approach.

### Annual health assessments

Annual health assessments take place at each school as far as possible during the same month of each year. The study team assess children in groups of four or five in a suitable room identified by the class-teacher, using standard protocols. Assessments take about 35 min per child and include:

Height, weight, body mass index (BMI).Pre- and post-bronchodilator spirometry.Annual study questionnaire for home completion by parents/guardians.

#### Spirometry

Following height (sitting and standing) and weight measurements, lung function is measured before and 15 min after bronchodilation, according to European Thoracic Society guidelines [30] by fully trained members of the study team using a Vitalograph 6000 Alpha Touch Spirometer, [31] calibrated using three litre precision syringe at the start of each session. Children inhale four puffs (100mcg/puff) of salbutamol *via* a large volume spacer, administered by a study team member. A new or sterilised spacer is used for each child.

#### Annual study questionnaire for home completion

Caregivers are asked to complete questionnaires in year 1 (when informed consent given to the study) and in study years 2, 3, 4 and 5. These comprise.

Demography and residential history.Parent-reported respiratory and allergy symptoms (ISAAC questionnaire) [32].Parent-reported paediatric quality of life (CHU9D questionnaire) [33].Non-NHS costs.Child absence from school.Smoking/exposure to second-hand smoke during pregnancy.Travel choices.Parental absence from work due to child ill-health.Upon receipt of a completed questionnaire, caregivers receive a £5 supermarket voucher.

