### Data

#### Statistical methods

The primary outcome variable of post bronchodilator FEV_1_, and secondary outcome variables of air pollution, post bronchodilator FVC and physical activity will be analysed longitudinally through a mixed effect model. The model assesses the interaction effect of time and study group to determine the difference in variable change between the intervention group (London) and comparison group (Luton). Mixed effects models using a random intercept term are robust to the biases of missing data and the clustering effect of recruiting participants from multiple schools, facilitating a longitudinal design in a highly transient population. Primary and secondary outcome variables will be adjusted to account for known covariates of gender, asthma diagnosis, ethnicity, deprivation, [38] age, height, and BMI. Secondary covariates which may be included after sensitivity analysis include socioeconomic status, stress, and physical activity. For linking air pollution data with lung function over time, a more complex mixed effect model with three levels will be used, the levels being child, school, and group. These will be tested first on a complete model with all levels, if models are not identifiable, then simpler models will be tried with fewer levels. These models would allow for the effects of each air pollutant to be tested against lung function at each level as well as over time.

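### Tobacco smoke exposure is collected by questionnaire but named in no covariate set for the London–Luton lung growth comparison

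*Protocol article*

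**What the plan says.** Under Annual study questionnaire for home completion, the article describes a repeated instrument: "Caregivers are asked to complete questionnaires in year 1 (when informed consent given to the study) and in study years 2, 3, 4 and 5". One of its listed topics is "Smoking/exposure to second-hand smoke during pregnancy".

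Under Statistical methods, the fixed adjustment set is stated as "Primary and secondary outcome variables will be adjusted to account for known covariates of gender, asthma diagnosis, ethnicity, deprivation, [38] age, height, and BMI". A reserve list follows: "Secondary covariates which may be included after sensitivity analysis include socioeconomic status, stress, and physical activity". The primary analysis is a mixed model, described as "The model assesses the interaction effect of time and study group to determine the difference in variable change" between London and Luton. A separate multilevel model links air pollutants to lung function.

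Table 1 has a row headed "Demography / potential confounding variables". Its source is the parent questionnaire in every study year, and its analysis column points to the interaction analysis. The row names no individual variable. The sections on sensitivity analyses and on additional analyses do not mention smoke.

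Under Study population and setting, Luton is justified as comparator by "broadly similar air quality, demography, and levels of socio-economic deprivation". Smoking is not among the features compared.

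**The concern.** The study compares two places that were not randomised and reads the difference in FEV1 growth as the effect of the policy. Household tobacco smoke acts on the same organ as traffic pollution, and the ULEZ is not expected to change it. If smoke exposure differs between the sites and slows growth, or if it changed differently over time (for example while families were at home during lockdowns), part of that difference enters the time-by-group term. The bias could run either way, producing an apparent benefit or hiding a real one.

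The pollutant–FEV1 models have the same gap. Their exposure is modelled ambient air at the home address, which does not measure smoke indoors.

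The study collects a smoke variable, and the article sets out both a fixed and a reserve covariate list. The omission is therefore visible in what is written, and it can be repaired without new data.

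**Working it through.** **1. Is smoke in the plan's adjustment?** Setting the places side by side:

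| Place in the article | Smoke named? |
|---|---|
| Questionnaire topics | Yes, one item |
| Fixed covariates, Statistical methods (seven) | No |
| Optional covariates, Statistical methods (three) | No |
| Table 1, potential confounders row | No variable named |
| Sensitivity and additional analyses | No |

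**2. Which smoke effects reach the primary contrast?** In a model with terms for group, time and group × time, a constant smoke-related difference in FEV1 level between the sites goes into the group term. Only a smoke-related difference in growth per year enters group × time. Adjustment for smoke as a main effect alone would therefore not be enough; it needs smoke × time.

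**3. The plan's own figures (Sample size).** 2 arms × 40 schools × 40 children = 3,200, as stated. The 90% power cannot be reproduced, because no standard deviation of FEV1 growth is given. The standard error that 90% power implies can be found without it. Sidedness is not stated, so I take two-sided 0.05:

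SE = 15 / (1.960 + 1.282) = 15 / 3.242 = 4.63 ml/year.

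**4. Size of the bias.** The documents give no smoke prevalence and no smoke effect. The following inputs are assumptions:

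- gap in the exposed share between sites, left after adjustment: 5 to 20 percentage points
- growth deficit in exposed children: 5 to 15 ml/year

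Bias b = gap × deficit.

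- Low end: 0.05 × 5 = 0.25 ml/year, and 0.25 / 15 = 1.7% of the target.
- Middle: 0.10 × 10 = 1.0 ml/year, and 1.0 / 15 = 6.7%.
- High end: 0.20 × 15 = 3.0 ml/year, and 3.0 / 15 = 20%.

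**5. What that does to the test.** With no true effect, the false-positive rate is 1 − Φ(1.960 − b/SE) + Φ(−1.960 − b/SE). With a true effect of 15 ml/year and a bias against it, power is Φ((15 − b)/SE − 1.960).

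| b (ml/year) | b/SE | False-positive rate | Power if the bias masks |
|---|---|---|---|
| 0.25 | 0.05 | 5.0% | 89% |
| 1.0 | 0.22 | 5.5% | 86% |
| 3.0 | 0.65 | 9.9% | 74% |

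The low end is negligible. The high end roughly doubles the error rate or costs about 16 points of power (90 − 74), but it needs the worst value of both assumed inputs.

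**The case against.** The strongest reply is that nothing in the article excludes smoke. Table 1 assigns questionnaire confounders as a class to the interaction analysis, the optional list is introduced with wording that need not be exhaustive, and a full covariate list is often left to an analysis plan, which is not shown here. This has some force, but it does not settle the matter. The article does more than defer: it names a fixed set and a reserve set. A covariate that might be added under an open-ended phrase is not pre-specified.

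Second, the sites were chosen for similar demography and deprivation, and deprivation and ethnicity are in the model. That should remove part of any confounding by smoke, and it makes the upper end of the assumed gap less likely. It does not show that smoke exposure is balanced.

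Third, the whole range of assumed bias lies below one standard error, and its direction is unknown. That stands, and it keeps the point modest.

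A reader might go further and infer from the listed topic that the questionnaire asks about smoke in pregnancy only, so that nothing is known about smoke during follow-up. The documents do not support that. The list is a summary of a form that is not shown. The covariate lists include stress and asthma diagnosis, and the topic list names neither of these. The slash in the smoke item also allows a wider reading: smoking in general, plus second-hand smoke in pregnancy. Nor does the article say that every topic is asked again each year.

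**Conclusion.** The point holds as an omission from the written adjustment: a collected, lung-specific exposure is named in neither covariate list for a non-randomised contrast. It could distort the London–Luton growth difference in either direction, and only through smoke-related differences in growth.

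Under the assumed inputs the bias is 0.25 to 3 ml/year, or 1.7% to 20% of the 15 ml/year target, against an implied standard error of about 4.6 ml/year. The bias range rests entirely on those assumptions. The standard error rests on the stated 90% power and a two-sided 0.05 test. The documents do not show that smoke exposure differs between the sites, so this is a possible bias and not a demonstrated one. I rate it as a cheap improvement worth making; it does not threaten the design.

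A case for adding new smoke questions to the questionnaire does not follow. The form is not shown. Recruitment opened in June 2018 and the article appeared in November 2023, so few rounds may remain, and an item first asked at the end would have no values for the earlier years.

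**What to change.** In Statistical methods, add the smoke exposure collected by the questionnaire to the pre-specified covariates, entered with its interaction with time. Do this in both the time-by-group comparison and the pollutant–FEV1 models. If the primary model is to stay as it is, make this a pre-specified sensitivity analysis at the least.

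If the questionnaire recorded current household smoke, use that variable. If it recorded only exposure in pregnancy, adjust for that, and report that confounding by current smoke remains.

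The cost is one or two sentences in the plan and no new data. The drawback is that some parents will not answer or will under-report, so the adjustment will be incomplete and missing answers will need handling.
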